## Abstract

**Background:**

Cognitive bias modification (CBM) interventions have demonstrated efficacy in augmenting core biases implicated in psychopathology. The current randomized controlled trial (RCT) will evaluate the efficacy of an internet-delivered positive imagery cognitive bias modification intervention for obsessive compulsive disorder (OCD) when compared to a control condition.

**Methods/Design:**

Patients meeting diagnostic criteria for a current or lifetime diagnosis of OCD will be recruited via the research arm of a not-for-profit clinical and research unit in Australia. The minimum sample size for each group (alpha set at 0.05, power at .80) was identified as 29, but increased to 35 to allow for 20% attrition. We will measure the impact of CBM on interpretations bias using the OC Bias Measure (The Ambiguous Scenarios Test for OCD ;AST-OCD) and OC-beliefs (The Obsessive Beliefs Questionnaire-TRIP; OBQ-TRIP). Secondary outcome measures include the Dimensional Obsessive-Compulsive Scale (DOCS), the Patient Health Questionnaire (PHQ-9), The Kessler Psychological Distress Scale (K10), and the Word Sentence Association Test for OCD (WSAO). Change in diagnostic status will be indexed using the OCD Mini International Neuropsychiatric Interview (M.I.N.I) Module at baseline and follow-up. Intent-to-treat (ITT) marginal and mixed-effect models using restricted maximum likelihood (REML) estimation will be used to evaluate the primary hypotheses. Stability of bias change will be assessed at 1-month follow-up.

**Discussion:**

A limitation of the online nature of the study is the inability to include a behavioral outcome measure.

**Trial registration:**

The trial was registered on 10 October 2013 with the Australian New Zealand Clinical Trials Registry (ACTRN12613001130752)

## Background

Cognitive bias modification is a cognitive experimental methodology that modifies cognitive biases via training conditions, in which participants are exposed to a series of stimuli designed to manipulate processing relevant to psychopathology. CBM interventions are either designed to modify attentional bias (CBM-A) or interpretive bias (CBM-I). Both forms have been shown to impact clinically relevant symptoms across a range of anxiety disorders and depression with effect sizes for CBM-I on biases ranging up to Hedges *g* = .81 (see reviews by Beard [1]; Hallion and Ruscio [2]; Macleod [3] Macleod and Matthews [4]). CBM-I interventions have demonstrated efficacy in modifying the key cognitive biases implicated in various anxious populations, including high trait anxiety [5,6], generalized anxiety [7], spider fear [8] and social anxiety [9-13]. This research has also extended to include transdiagnostic constructs such as perfectionism, which is associated with a range of clinical diagnoses [14]. Importantly, some studies have shown that the resultant change in selective information processing due to CBM-I interventions impacts emotional responses to subsequent stressor tasks [7,14-17], as well as relevant anxiety symptoms [12,13,16].

CBM-I procedures may have particular relevance in the context of obsessive compulsive disorder (OCD), given that prominent cognitive models of the disorder assert that intrusive thoughts are experienced by most people, but develop into obsessions when appraised (interpreted) as posing a threat for which the individual is personally responsible. Research has identified a series of belief domains from which these negative interpretations arise [18] (OCCWG, 2005): overestimation of threat, inflated responsibility, perfectionism, intolerance of uncertainty, importance of thoughts, and the need to control thoughts. Correlational evidence supports the association between biased interpretations of intrusive thoughts and obsessive-compulsive symptoms [18-21]. Prospective studies have even demonstrated that negative interpretation of intrusive thoughts at baseline predicts OCD symptom severity at follow-up [22,23].

Currently, cognitive-behavioral therapy (CBT) is the primary treatment of OCD. However, response rates are only 50% when drop-out rates are considered [24], implying a clear need for treatment advancements. CBM-I procedures are gaining increasing research attention in association with OCD and high OC symptoms, with evidence now emerging for their impact on interpretation biases, emotional and physiological responses to OC stressors, and subsequent behavior (detailed below). In addition, CBM-I interventions for OCD have been shown to effect change specifically by altering contingency learning about potential threat cues [25], rather than via habituation of fear and arousal as hypothesized for exposure-based interventions.

The most common CBI-I method - utilized in the current study - involves ‘ambiguous scenario training’. Developed by Matthews and Mackintosh [26], the method involves presenting participants with a serious of scenarios that are ambiguous in terms of potential threat. Each scenario ends with a word fragment, which the participant is asked to complete in order to resolve the ambiguity in either a positive (non-threatening) or negative (threatening) way. Repeatedly pairing a potential anxiety trigger with a benign interpretation is proposed to train contingencies between ambiguous (potentially threatening) cues and positive interpretations. This particular method has been used to effect change in interpretation bias across various anxious samples [5,8,11,27].

Clerkin and Teachman [28] first applied this method to obsessive-compulsive (OC) beliefs, evaluating whether participants high in OC-symptoms could be trained to adopt healthier interpretations of OC-related information, across a variety of OC-relevant domains. They also tested whether the ambiguous scenario training influenced participants’ responses to an OC-stressor task (designed to elicit distress and the urge to engage in a compulsion or neutralization behavior). As hypothesized, participants in the positive CBM-I training condition endorsed healthier OC-relevant interpretations (Cohen *d* = .76) and beliefs (*η*^2^*p* = .07) following training versus those in a neutral CBM-I control condition (in which half the scenarios resolved positively and half resolved consistently with OC-beliefs). Those in the positive training condition also reported less negative emotion (at trend level) during the subsequent stressor task, providing initial evidence that modifying interpretation biases in a high OC-population may have downstream effects on emotional and physiological responses to OC-stressors.

To extend these results, Grisham *et al*. [29] used CBM-I to specifically target and modify interpretive bias reflecting inflated responsibility in a sample of undergraduate students with high levels of checking symptoms. Participants were randomly assigned to a Positive (decreasing responsibility interpretations) or Negative (increasing responsibility interpretations) training condition. Although there were no differential effects with respect to observed or self-reported checking or self-reported responsibility beliefs, participants in the Positive training condition did demonstrate reduced responsibility bias in a subsequent interpretive bias test (ηp^2^ = .07), as well as more adaptive physiological responding during a responsibility stressor task (ηp^2^ = .12), compared to the Negative training condition. In a broader study, Williams and Grisham [30] evaluated a CBM-I training paradigm in a sample of community members with varying levels of OC symptoms. The impact of CBM was assessed using measures of interpretation bias, distress, and responses to three behavioral tasks designed to tap the core belief domains implicated in OCD: importance of thoughts/control, perfectionism/intolerance of uncertainty, and contamination/estimation of threat. Participants randomly assigned to the active CBM condition evidenced a change in interpretation bias, endorsing more positive and less negative OC-relevant interpretations compared to participants assigned to the CBM control condition (Cohen’s *d* ES = .66). Importantly, there was not a corresponding shift in interpretive bias to foil scenarios (those unrelated to the core OC belief domains), suggesting specificity in the CBM-I training effect rather than a general positivity bias. Similar to earlier findings [29], there was no significant difference in terms of behavioral responses to the OC stressor tasks, but participants in the Positive condition did report significantly less distress and urge to neutralize following the OC stressor task designed to tap importance of thoughts/control.

Based on these collective results, CBM procedure may hold promise as a means to selectively target OC beliefs, reduce interpretive biases, and lead to changes in emotional responses associated with OC symptoms. However, these results need to be replicated in clinical samples, with adequate follow-up, in order for potential therapeutic benefits to be demonstrated for OCD.

The current SPIRIT-compliant [31] protocol (see Table 1) outlines the methodology of a randomized controlled trial (RCT) to establish the efficacy of a CBM intervention for participants who meet current diagnostic status for OCD when compared to an active CBM control condition. In order to investigate whether previously symptomatic individuals demonstrate a negative interpretation bias for OC-specific information, participants with a lifetime diagnosis of OCD will also be recruited for secondary analyses.

**Table 1 T1:** Items from the World Health Organization trial registration data set

**Secondary identifying numbers**	**ACTRN12613001130752**
Source(s) of monetary or material support	
Primary sponsor	St Vincent’s Hospital, Sydney
Secondary sponsor(s)	
Contact for public queries	AW, GA
Contact for scientific queries	AW, GA
Public title	Cognitive Bias Modification (CBM) and Obsessive Compulsive Beliefs
Scientific title	Randomized controlled trial comparing Internet-based cognitive bias modification (active version) for obsessive compulsive disorder versus Internet based cognitive bias modification (control version) on negative interpretation bias.
Countries of recruitment	Australia
Health condition(s) or problem(s) studied	Obsessive Compulsive Disorder
Intervention(s)	Experimental: CBM Version A (Active treatment)
	CBM Version A is an Internet-based intervention taking place over 1 week.
	Placebo Comparator: CBM Version B (Control)
	CBM Version B (Control) is an Internet-based intervention taking place over 1 week (identical to CBM Version A without the putative active components).
Key inclusion and exclusion criteria	Inclusion: 18 to 65 years of age; Meet Diagnostic and Statistical Manual of the American Psychiatric Association - 4th edition (DSM-IV) criteria for current or lifetime Obsessive Compulsive Disorder; Internet and printer access; Australian resident; fluent in written and spoken English
	Exclusion: Current substance abuse/dependence; Psychotic mental illness (Bipolar or Schizophrenia); change in medication or psychological treatment during last 1 month or intended change during study duration; use of Benzodiazepines, severe depression (PHQ9 > 23), Suicidal (PHQ9 item 9 > 2)
Study type	Interventional
Date of first enrollment	24 October 2013
Target sample size	70
Recruitment status	Recruiting
Primary outcome(s)	Change in: Interpretations bias (the Ambiguous Scenarios Test for OCD; AST-OCD), the Word Sentence Association Test for OCD (WSAO), and the OC Bias measure.
Key secondary outcomes	Change in: The Obsessive Beliefs Questionnaire-TRIP (OBQ-TRIP), the Patient Health Questionnaire (PHQ-9); the Dimensional Obsessive-Compulsive Scale (DOCS). Change in diagnostic status will be indexed using the OCD M.I.N.I Module at baseline and follow up.

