#### The obsessive beliefs questionnaire-TRIP [33]

The OBQ-TRIP (20-item version) is a factor-analytically derived brief version of the original Obsessive Compulsive Cognitions Working Group (OCCWG) 44-item version [18]. Each of the 20 items designed to measure cognitions and beliefs central to OCD are rated on a 7-point Likert-type scale (1 = disagree very much to 7 = agree very much). The OBQTRIP- 20 correlates well with the full OBQ-TRIP and demonstrates good internal consistency, Cronbach’s alpha = .77 to .82 [18]. The OBQ-TRIP will be collected at baseline, following the 1-week CBM intervention, and at 1-month follow-up.

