#### The word sentence association test for obsessive compulsive disorder [39]

The WSAO is a measure of interpretation bias in OCD, comprising of 20 distinct ambiguous obsessive-compulsive (OC)-related sentences across multiple domains of OC symptoms. Ten sentences are followed by an OC-related threat word and ten are followed by a benign word. Participants are instructed to indicate how related the sentence and the word are to each other. For example, participants see the sentence ‘Part of the floor you are walking on is brown*’* and then circle how related the sentence is to the word ‘excrement’ (threat word). Participants also see ambiguous sentences paired with benign words, such as ‘There were many appliances running when you left*’* and rate how related the sentence is the word ‘busy’. Higher ratings of relatedness for threat words to the ambiguous sentences compared to ratings of relatedness of benign words to the ambiguous sentences reveals a threat interpretation bias on this measure. Internal consistency is good (a = .81) for the total measure. The WSAO will be collected at baseline, following the 1-week CBM intervention, and at 1-month follow-up.

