### Ethics and dissemination

The current trial protocol has been approved by the Human Research Ethics Committee (HREC) of St. Vincent’s Hospital and the University of New South Wales, Sydney. The trial is registered as ACTRN12613001130752. No protocol amendments have been made.

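### Table 1 and the Methods name different primary outcomes: WSAO and OBQ-TRIP trade places, and no amendment explains it

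*Protocol article*

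**What the plan says.** **Table 1 (Background), the registration data set.** The primary outcomes are change in the AST-OCD, then "the Word Sentence Association Test for OCD (WSAO), and the OC Bias measure". The key secondary row opens with "Change in: The Obsessive Beliefs Questionnaire-TRIP (OBQ-TRIP), the Patient Health Questionnaire (PHQ-9") and goes on to the DOCS and M.I.N.I. diagnostic status.

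**Methods/Design.** Three instruments stand under the primary outcome heading: the OC Bias Measure, the AST-OCD and the OBQ-TRIP, the last introduced with "The OBQ-TRIP (20-item version) is a factor-analytically derived brief version". Under the secondary heading come the DOCS, the PHQ-9, the WSAO ("The WSAO is a measure of interpretation bias in OCD"), the K10 and diagnostic status.

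**Abstract.** The effect of training is to be measured "using the OC Bias Measure (The Ambiguous Scenarios Test for OCD ;AST-OCD) and OC-beliefs (The Obsessive Beliefs Questionnaire-TRIP; OBQ-TRIP"). The next sentence begins "Secondary outcome measures include the Dimensional Obsessive-Compulsive Scale (DOCS), the Patient Health Questionnaire (PHQ-9") and ends its list with the K10 and the WSAO.

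**Ethics and dissemination; Trial status.** "No protocol amendments have been made". At submission on 6 January 2014, 28 participants had been randomised.

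**The concern.** A primary outcome list protects a trial only if there is one list. Here the instrument in the third primary place depends on which section is read. The two candidates measure different things: the WSAO measures interpretation bias, the OBQ-TRIP measures obsessive beliefs. If training shifted one and not the other, an author could cite Table 1 or the Methods, each in good faith, for whichever gave the clearer result. Once group comparisons have been seen, nobody could show that the choice came first.

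**Working it through.** The check is a comparison of text. No sample-size or power figure changes with it.

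**Step 1. Set the lists side by side.**

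| Instrument | Abstract | Table 1 | Methods |
|---|---|---|---|
| OC Bias Measure | implied primary, merged with AST-OCD | primary | primary |
| AST-OCD | implied primary, merged with OC Bias Measure | primary | primary |
| OBQ-TRIP | implied primary | key secondary | primary |
| WSAO | secondary | primary | secondary |

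Table 1 and the Methods each name three primary measures and share two. The measures called primary in at least one place therefore number 3 + 3 − 2 = 4. The Abstract never labels its list as primary. It names the OBQ-TRIP before the secondary list begins and puts the WSAO inside that list, so on the two disputed measures it sides with the Methods.

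**Step 2. Are the OC Bias Measure and the AST-OCD one instrument, as the Abstract writes?** No. The Methods describe the first as ten scenarios followed by sentences rated for similarity of meaning from 1 to 4. They describe the second as 12 scenarios rated for valence and for arousal from 1 to 7. Table 1 also lists them separately.

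**Step 3. Does anything else in the article settle which list holds?**
- *Amendments:* none reported, so no logged change links the two lists.
- *Titles (Table 1):* the scientific title speaks of negative interpretation bias, which fits the WSAO. The public title speaks of obsessive compulsive beliefs, which fits the OBQ-TRIP.
- *Hypotheses:* for the lifetime-diagnosis group, the WSAO is grouped with the AST-OCD and the OC bias measure, as in Table 1. For current OCD, the prediction joins bias with symptoms and names no instrument.
- *Statistical methods:* primary hypotheses are mentioned without naming the outcomes that carry them.
- *Sample size:* the stated 29 per group reproduces for the larger of the two quoted effects. With d = 0.76, two-sided alpha 0.05 and power 0.80, the normal approximation is n = 2(1.960 + 0.842)²/0.76² = 15.70/0.5776 = 27.2, so 28. The two-sample t-test gives 28.17, so 29. Then 29 × 1.2 = 34.8, so 35. The Background describes the effects of .66 and .76 as effects on interpretation, but the calculation names neither the WSAO nor the OBQ-TRIP. It does not decide between them.

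These clues point in different directions, and none is a statement of the primary set.

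**Step 4. Can the two constructs part company?** The Background cites one study in which both interpretations and beliefs became healthier after positive training. It cites another in which an interpretive bias test favoured positive training while self-reported responsibility beliefs showed no differential effect. The second compared positive with negative training in students, which is not this trial's contrast. It shows that divergence is possible, not that it is expected here.

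**The case against.** The strongest reply is that this is a drafting slip of limited reach. The OC Bias Measure and the AST-OCD are primary in both lists. The Abstract and the Methods agree on the other two measures, so a reader may take the Methods as authoritative and Table 1 as out of step. An analysis plan that is not shown may name the primary set.

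Part of this stands. It may well be a slip, and the core of the primary set is stable. But Table 1 is presented as the registration data, which is where a reader looks to check pre-specification. An analysis plan could settle the matter only by contradicting one of the two sections. This is a statement made twice and differently, not a detail left out of a condensed article.

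Four stronger readings are tempting and go beyond the documents:
- *That there are three rival primary sets.* On the OBQ-TRIP and the WSAO there are two. The Abstract's added fault is merging two instruments.
- *That the OBQ-TRIP is the weaker or underpowered candidate.* The Background gives a partial eta-squared of .07 for beliefs in one cited study, but also .07 for an interpretive bias test in another. It gives no effect size for the WSAO. The instruments cannot be ranked on this evidence, and converting such a value to a two-group power figure would ignore the planned repeated-measures mixed model.
- *That the sample size was built on the OC Bias Measure.* The Methods attribute that measure to the study that gave .76. Nothing says that .66 came from it, so this remains an inference.
- *That outcomes were switched after enrolment began.* Nothing in the article shows this.

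**Conclusion.** The contradiction is in the text and should be removed before any unblinded comparison. Its size is one of three primary places, filled by the WSAO in Table 1 and by the OBQ-TRIP in the Methods, plus an Abstract that blurs the two measures on which both lists agree. The conclusion assumes only that the headings in the Methods and the row labels in Table 1 mean what they say, and that the Abstract implies its primary list by position.

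A reader might infer that the trial will be positive or negative according to the page followed. That is possible but not shown: it needs the two measures to give different results. Nor would choosing a list by itself say which result or results decide success. That rule may stand in an analysis plan, and its absence from the article is not part of this point.

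**What to change.** 1. Before any comparison by arm, agree one primary list, date it, and use it in the Abstract, Table 1, the Methods and the registry entry.
2. Name the OC Bias Measure and the AST-OCD as two instruments in the Abstract.
3. Record the step for what it is. If one section was misprinted, issue a dated correction. If the primary set changed, log an amendment and revise the no-amendments statement.

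For the content of the list, a neutral default is to keep as primary only the two measures that both Table 1 and the Methods name, with the OBQ-TRIP and the WSAO both secondary. This favours neither disputed measure. The documents do not require it, and the sponsor may choose otherwise if the choice is made and dated while still blind to results.

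The cost is an editorial correction and a registry update. Both disputed measures are already collected at baseline, after training and at 1-month follow-up, so no data collection changes.

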### Hypotheses

For participants who meet diagnostic criteria for current OCD, we predict that CBM active training, relative to CBM control training, will result in a bias towards more positive OC-specific targets and a reduction in OC symptom measures. We further predict that benefits will be maintained at 1-month follow-up. For participants who meet criteria for a lifetime diagnosis of OCD (and do not meet criteria for current OCD) and who evidence a negative interpretation bias at baseline, we predict that CBM active training, relative to CBM control training, will result in a bias towards more positive OC-specific targets (OCD-Bias measure) and bias scores (AST-OCD; WSAO). We do not predict a significant change in measures of OC symptoms (DOCS) in individuals with a lifetime diagnosis.

## Methods/Design

### Trial design

The trial is a randomized controlled superiority trial with two parallel arms.

### Study setting

The Clinical Research Unit for Anxiety and Depression (CRUfAD) is a not-for-profit joint initiative of St. Vincent’s Hospital and the University of New South Wales, School of Psychiatry in Sydney, Australia. CRUfAD specializes in the development, evaluation, and dissemination of evidence-based CBT programs via the Internet. The mode of Internet recruitment and delivery enables potential participants from all Australian states to be eligible to apply for enrollment in the current trial.

### Participants and recruitment

Power calculations were informed by calculation of effect size data from Williams and Grisham [30] and Clerkin and Teachman [28] providing between-group effect sizes of .66 and .76, respectively. The minimum sample size for each group meeting current diagnostic status (alpha set at 0.05, power at .80) was identified as 29, but is set at 35 to hedge against expected attrition of up to 20%. Participants will be recruited via the research arm of a not-for-profit clinical and research unit affiliated with St. Vincent’s Hospital and the University of New South Wales, Australia.

Potential participants will be recruited from the community and from previous research trials via advertisements placed on local mental health websites, in newsletters, and in printed newspapers. Applicants will be directed to the Virtual Clinic website (http://www.virtualclinic.org.au) where they first complete automated online screening questionnaires about symptoms and demographic details (see Figure 1). Inclusion criteria are as follows: meet diagnostic criteria for current or lifetime Obsessive Compulsive Disorder; has Internet and printer access; is an Australian resident; and is fluent in written and spoken English. Exclusion criteria are as follows: is a non-resident of Australia; is less than 18 or older than 65 years of age; is currently receiving CBT for OCD; has severe depression and (PHQ9 > 23)/ or suicidal ideation (PHQ9 item 9 = 3); has drug or alcohol dependence; has a psychotic disorder or is taking atypical antipsychotics or benzodiazepines; and if taking medication for anxiety or depression, has been taking the same dose for less than 1 month or intends to change the dose during the course of the program. Excluded applicants receive information on alternative services and are encouraged to discuss their symptoms with their physician.

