### Primary outcome measures

#### The Obsessive Compulsive bias measure [28]

To obtain an index of interpretation bias both before and after CBM-I training, the bias measure designed by Clerkin and Teachman [28] will be employed. Participants are first exposed to ten scenarios with a missing letter in the final word of the sentence. Each scenario remains ambiguous in nature even after completion of the word fragment (for example, ‘You are driving to visit friends who live several hours away. Outside, it begins to rain and you are careful to drive the speed limit. You think about the importance of driving s_fely’). In this example, the letter ‘a’ would be required to complete the word stem of ‘safely’. Following the filler task (below), participants are randomly presented with four sentences and required to rate how similar each was to the meaning of the scenario they previously imagined themselves in (1 = very different in meaning to 4 very similar in meaning). Each sentence corresponds with four different interpretations, none of which was worded identically to the sentence in the paragraph they had previously imagined themselves in. OC-positive scenarios are consistent with a response that challenges the core maladaptive belief (for example, ‘As you drive down the road, you think your chances of getting into an accident are low because you are being so cautious’) whereas OC-negative scenarios are those consistent with a response that reinforces the core maladaptive belief (for example, ‘*As you drive down the road, you worry that you’ll accidentally crash your car even though you aren’t speeding’*). Foil scenarios are included to assess for a general interpretation bias. Foil Positive scenarios are positive, but unrelated to core OC maladaptive beliefs (for example, ‘*As you drive down the road, you are looking forward to visiting your friend’*) and Foil Negative scenarios are negative, but also unrelated to OC beliefs (for example, ‘As you drive down the road, you are not looking forward to visiting your friend*’*). Cronbach’s alpha for the indices ranges from .68 to .79. The OC Bias Measure will be administered at baseline, following the 1-week CBM intervention, and at 1-month follow-up.

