#### Ambiguous Scenarios Test-obsessive compulsive disorder

The AST-OCD (AW and JG, unpublished work) is a measure of interpretation bias comprising 12 ambiguous scenarios designed to tap the following belief domains: intolerance of uncertainty, perfectionism, threat estimation, control of thoughts, responsibility, and importance of thoughts. Each belief domain comprises two items. Items are rated in terms of their emotional valence (1 = very negative to 7 = very positive) and their associated arousal (1 = very anxious to 7 = very excited). Scores are averaged to form a total score of valence and arousal. Participants are asked to imagine each of the scenarios and imagine the event happening to them (for example, ‘Your partner has taken you to a new restaurant for dinner. Before you eat, you visit the restroom and notice it is unusual’). The AST-OCD will be collected at baseline, following the 1-week CBM intervention, and at 1-month follow-up.

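### Three unranked primary instruments, listed differently in two places, share a sample size that covers one comparison at 0.05

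*Protocol article*

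**What the plan says.** **Primary outcomes.** Under Primary outcome measures the protocol article describes the OC Bias Measure, the AST-OCD and the OBQ-TRIP, and puts none of them first. Table 1 also names three primary instruments, but they are the AST-OCD, the WSAO and the OC Bias Measure; the OBQ-TRIP is a key secondary there. The body text reverses this and places the WSAO under Secondary Outcome Measures. The Abstract adds a further ambiguity by giving the AST-OCD as though it were the name of the OC Bias Measure.

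**Scores.** The OC Bias Measure asks for ratings of several sentences per scenario ("Each sentence corresponds with four different interpretations"): OC-positive, OC-negative and two foils. For the AST-OCD, "Scores are averaged to form a total score of valence and arousal". No scoring is given for the OBQ-TRIP.

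**Time points.** All three instruments are taken three times. For example, "The OBQ-TRIP will be collected at baseline, following the 1-week CBM intervention, and at 1-month follow-up". None of these times is named as primary.

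**Sample size.** Participants and recruitment cites two earlier studies "providing between-group effect sizes of .66 and .76, respectively", and sets "alpha set at 0.05, power at .80". The minimum per group "was identified as 29, but is set at 35 to hedge against expected attrition of up to 20" per cent. The section does not say which effect size was used or whether the test is one- or two-sided. Trial design says only: "The trial is a randomized controlled superiority trial with two parallel arms".

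**Analysis.** Statistical methods specifies mixed models, with before-after contrasts where an effect is significant. It gives no order among outcomes, no division of alpha and no rule for calling the trial positive.

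**The concern.** Choosing the primary outcome and sizing the trial for it are protocol decisions. Here the choice is left open among three instruments, and the two lists disagree about which three. The sample size allows for only one comparison at 0.05.

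Two things are at stake. If a significant result on any one primary measure were taken as success, the false-positive rate would exceed the nominal 5%. If a correction were added later to prevent that, the trial would no longer have its stated 80% power. In addition, a reader of the results could not tell which outcome was meant to decide the question, because the article supports two answers.

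**Working it through.** **Inputs from the protocol article:** alpha 0.05; power .80; effect sizes .66 and .76; 29 per group, set at 35; attrition up to 20%. **Assumed, because the article does not give them:** a two-sided test, correlations between primary scores of 0 to .9, and the success rules named below.

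**1. The plan's own figure.** With the normal approximation, n per group = 2(1.960 + 0.842)² / d².
- d = .76: 2 × 7.85 / 0.5776 = 27.2, so 28. The exact t-test needs 28.17, so 29, which matches the plan.
- d = .66: 2 × 7.85 / 0.4356 = 36.0, so 37. The exact t-test needs 37.02, so 38.
- A one-sided test at d = .66 also gives 29 by the normal approximation (28.4 rounded up; 30 by t-test).

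On either route to 29, the figure is for one comparison at an undivided 0.05. The step to 35 is 29 × 1.2 = 34.8, rounded up. A 20% loss from 35 leaves 28 completers per arm, which is used below.

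**2. False-positive rate if each primary is tested at 0.05 and any one counts.** For k independent tests it is 1 − 0.95^k: 1 − 0.857 = 14.3% for k = 3, and 1 − 0.774 = 22.6% for k = 5. For equal correlation ρ it is 1 − ∫ φ(u) [Φ((1.96 − √ρ·u)/√(1 − ρ)) − Φ((−1.96 − √ρ·u)/√(1 − ρ))]^k du. Both directions are counted, as in the nominal 5%.

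| Tests | ρ = 0 | ρ = .5 | ρ = .7 | ρ = .9 |
|---|---|---|---|---|
| 3 (one per instrument) | 14.3% | 12.5% | 10.9% | 8.4% |
| 5 (two OC Bias indices, AST valence, AST arousal, one OBQ-TRIP score) | 22.6% | 18.3% | 14.8% | 10.2% |

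The three-test row is the same for either list of primaries, since both have three instruments.

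**3. Power if Bonferroni over three is applied** (alpha 0.05/3 = 0.0167, two-sided t-test, 28 per arm).

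| d | alpha 0.05 | alpha 0.0167 | Completers per arm for .80 at 0.0167 |
|---|---|---|---|
| .76 | .80 | .65 | 38 |
| .66 | .68 | .50 | 50 |

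At d = .66 power is already .68 before any correction. Only the drop from .68 to .50 is due to multiplicity; the gap from .80 to .68 comes from the effect size.

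**4. If all three primaries had to be significant.** The error rate would then be at most 5%. With equal effects, power at 28 per arm would be .80³ = .51 at d = .76 and .68³ = .31 at d = .66 for independent scores. At correlation .7 it would be about .66 and .50.

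**The case against.** The strongest objection is that the protocol does not say what a reader might infer from it, namely that every primary score is tested at 0.05 and that any one significant score shows efficacy. The value 0.05 appears only in connection with the sample size, and Statistical methods states no success rule. The Hypotheses section predicts a bias shift together with a symptom reduction for current OCD, which reads more like a joint prediction. Under a rule that all must succeed, there is no inflation. This stands: the percentages in step 2 are conditional and are not a stated property of the plan.

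A reader might also infer five primary tests and take 23% as the error rate. The article does not support that as fact. It does not say that OC-positive and OC-negative ratings are tested separately, its sentence on AST-OCD scoring could mean one total or two, and a single OBQ-TRIP score is an assumption. The 22.6% also needs five independent scores, which is unlikely for related measures in the same patients. It is the upper end of the five-score range.

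Thirdly, a multiplicity procedure and detailed score definitions are commonly left to a statistical analysis plan, and one may exist. This stands for the procedure. It does not remove the two conflicting lists or the sizing for a single comparison, both of which are printed here. A later plan could add a correction, but that would not restore power to a sample sized without one.

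Finally, the power figures are for a plain t-test and not for the planned repeated-measures model. That model could do better, but the article gives no correlation from which to work this out. The figures show the size of the loss; they do not predict the trial's actual power.

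**Conclusion.** The point holds in this form: the primary outcome is not fixed, two lists of primaries conflict, and the sample size covers one comparison at 0.05.

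Its size depends on the rule eventually used. With any one result counting at 0.05, false primary success is about 8–14% for three tests and 10–23% for five scores, over assumed correlations of .9 to 0. With Bonferroni over three, power at 28 completers per arm is .65 at d = .76 and .50 at d = .66. With all three required, error is controlled but power falls below .80 at both effect sizes for the correlations shown. None of these ways of treating three primaries gives both 5% error and the stated power; a single primary or an ordered sequence avoids the conflict. The documents do not support saying that the trial's false-positive rate is any particular figure. This should be corrected, and correcting it needs no more participants.

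**What to change.** Reconcile Table 1 with the outcome sections, including the places of the WSAO and the OBQ-TRIP, and correct the Abstract where it merges the OC Bias Measure with the AST-OCD. Then, before outcome analysis, name one primary outcome, one score and one time point in participants with current OCD.

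The natural choice is the OC Bias Measure's OC-target interpretation score at post-training, because the effect sizes cited for power (.76 and .66 in Background) are for OC-relevant interpretations. The investigators need to define how it is scored, since the article does not say which score those effect sizes refer to. The choice of outcome remains theirs.

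Test any further confirmatory outcome in a fixed sequence, each at 0.05 and only if the one before it is significant, and make the rest secondary. Alternatively, keep three primaries with Holm's procedure and restate the power.

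The cost is protocol wording, a registry update and fewer outcomes that can be called confirmatory. The single-primary route needs no extra participants. Keeping three primaries means accepting lower power or enlarging the sample: on a Bonferroni basis, 38 completers per arm at d = .76 or 50 at d = .66, against 28.
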